### Population

Multi-trauma patients admitted to one of the accident & emergency departments (A&E) of the participating hospitals are included. Multi-trauma is defined as having at least 2 or more injuries of which at least 1 is life threatening, including a) trauma with an Injury Severity Scale score ISS > = 16, b) complex multiple injuries on both lower extremities, c) a combination of one upper and one lower extremity injury, the latter of which can not be used in load-bearing, or d) complex pelvis/acetabulum fractures (for in- and exclusion criteria see Table 1)

**Table 1 T1:** Inclusion and exclusion criteria

Inclusion criteria	Age > = 18 years
	Multi-trauma (as defined above)
	Hospitalisation after A&E admission
	Rehabilitation indication, i.e. lasting impairments or handicaps are expected
	Adequate Dutch language skills
Exclusion criteria	Severe alcohol and/or drug abuse
	Severe psychiatric problems

A&E: Accident and Emergency room

Participants for the SFTRS will be recruited in the adherence of the trauma centre in the south of the Netherlands. The reference group will be recruited in the adherence of one of the other trauma centres in the Netherlands. The inclusion of the participants will start in October 2008 and will continue until May 2010. Both medically and ethically it is not feasible to randomise the acute multi-trauma patients across the two trauma centres mainly due to geographical distances. Therefore, a non-randomised controlled clinical trial is used.

Based on the 2005–2007 databases from the participating centres, the influx numbers for the SFTRS group and the CTCS group are expected to amount to about 364/year and 370/year respectively. Prospective data from a pilot study in 2008 showed that, within 3.5 months, in each of the two centres 86 multi-trauma patients were admitted to the A&E. Given an inclusion period of 19 months, approximately 467 patients in each of the respective regions are expected, totalling 934 for this study (see flow chart, Figure 1).

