### Data collection

Baseline measurements will be administered as soon as possible post-injury (= T0). Further measurements will be taken at 3 months (= T1), 6 months (= T2), 9 months (= T3) and 12 months (= T4) post-trauma (see also flow chart, figure 1).

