### Determination of costs

General considerations:

For the economic evaluation the main research question is:

From the viewpoint of the society is another organisation of professional care service for trauma patients (i.e. SFTRS) compared to CTCS preferable in terms of costs, effects and utilities?

Based on this main research question several sub-questions are relevant:

1) What are the costs of SFTRS compared to CTCS preferable in terms of costs, effects and utilities?

2) What are the extra effects (measured in quality of life, utilities, and saving by reducing inpatient hospital admissions of multi-trauma patient) of SFTRS compared to CTCS preferable in terms of costs, effects and utilities?

We hypothesise that SFTRS is associated with a reduction in health care and patient costs, and an improvement in quality of life, compared to CTCS. We expect SFTRS to be cost-effective from a societal perspective. Assessments of the quality of life and costs will take place at T1 through T4.

In the cost identification, the following costs are considered:

Health care costs: cost of the intervention program and other health care resources both by the patient and the caregiver.

• Patient and family costs: informal care, paid domestic help, transportation, over the counter medication, and other out-of-pocket expenses.

• Production losses: absenteeism, presenteeism (loss of productivity while at work), and compensation mechanisms for both the patient and the caregiver, if relevant.

Measurement of volumes:

• Hours spent on the intervention program will be recorded on a pre-structured form by the acting healthcare professionals.

• All other health care costs and patient & family costs will be recorded in a cost questionnaire.

• Production losses will be measured using the patient modules of the PRODISQ [43,44].

The PRODISQ will be used together with the costs questionnaire, every 3 months at baseline and T1 through T4.

For the valuation of health care costs and patient & family costs, an update of the Dutch manual for costing in economic evaluations [45] will be used. For care for which no costs-guidelines are available estimations of the costs will be made, based on the real costs and/or on population based estimates from literature. Valuation of production losses will be based on a modification of the friction cost method

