Both generic Quality of life (QoL) and utilities are derived from the SF-36. An overall utility score for population based QoL can be obtained, which facilitates comparisons with other interventions, i.e. the social tariff of the SF-36 [28-33].

The primary outcome measure for the cost-effectiveness analysis will be FIM. The primary outcomes measure for the cost-utility measure will be utilities based on the SF-36 social tariff.

The time horizon is 12 months. Ratios will be determined, based on incremental costs and effects of SFTRS compared to CTCS. The cost-effectiveness ratio will be stated in terms of costs per improvement on the FIM. The cost-utility ratio will focus on the net cost per QALY gained. Bootstrap re-sampling techniques [46,47] are used to explore cost-effectiveness uncertainty.

Sensitivity analyses will be performed for the costs that turn out to have the largest impact on the differences in total costs between SFTRS and CTCS. In these analyses both the variance in volumes and prices will be considered. The range over which uncertain factors are thought to vary will be assessed by calculating a minimum and maximum (mean value of costs minus or plus the SD).

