### Statistical analyses

In non-randomised comparative studies, variations in case mix between centres can influence the interpretation of outcome data [48]. Therefore, for each of the data sets collected at T1 through T4, differences in outcome variable between the 2 services will be tested using multiple MANCOVA's, entering various indicators of case mix as co-variates, i.e. age, gender, ISS, number of complications, pre-trauma psycho-social status.

When patients drop out of the study, the reason for their withdrawal will be recorded. Drop-outs may bias the treatment effect evaluations. Therefore, the following regime will be applied:

- Missing T4 measurement: 'last-observation-carried-forward' principle will be applied.

- Missing T3 or T2 measurement: linear interpolation of data using data from adjacent time points (e.g. T1 and T4) for imputation.

- Missing T0 or T1 measurement or more than 2 missing measurements: discarding of patient data and influx of additional patient in order to meet n = 82 per group.

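### The missing-data rules make no exception for death, so, applied as written to the 12-month cost-utility analysis, they never count a death as QALY loss

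*Protocol article*

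**What the plan says.** Under Determination of costs, the article sets the cost-utility outcome: "The primary outcomes measure for the cost-utility measure will be utilities based on the SF-36 social tariff", and "The cost-utility ratio will focus on the net cost per QALY gained". It adds: "The time horizon is 12 months". The visit schedule, under Data collection, is: "Further measurements will be taken at 3 months (= T1), 6 months (= T2), 9 months (= T3) and 12 months (= T4) post-trauma".

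Under Statistical analyses, one regime covers measurements that are absent after drop-out:

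- "Missing T4 measurement: 'last-observation-carried-forward' principle will be applied".
- A missing T2 or T3 is filled by linear interpolation between neighbouring time points.
- If T0 or T1 is missing, or more than two measurements are missing, the instruction is "discarding of patient data and influx of additional patient in order to meet n = 82 per group".

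The outcome, cost and statistical sections do not mention death. Under Population, multi-trauma is defined as "having at least 2 or more injuries of which at least 1 is life threatening", followed by a list of qualifying injury patterns.

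**The concern.** A QALY combines length of life with its quality. After death the utility is known to be 0; it is not a missing value to be estimated. The rules are triggered purely by which visits are absent, and a patient who has died has absent visits. If nothing exempts that patient, the QALY total reflects quality of life only, among people who lived to T2, with some of them credited for time when they were dead. A better imputation method would not cure this, because it would still produce utilities for the dead.

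Allocation is by trauma centre and is not randomised, so survival could differ through case mix or through the service itself. The article says the results bear on whether SFTRS should be introduced nation-wide. A cost-utility ratio that cannot record lost life-years would be a weak basis for that.

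**Working it through.** **Step 1. The plan's own figure.** The only relevant stated number is 82 per group. The target difference is 15% of 30.2 = 4.53 motor FIM points, with SD 9.5, two-sided 5% and 80% power. The normal approximation 2 × (1.960 + 0.842)² × 9.5² / 4.53² gives 69.0, hence 70. The t-based solution is 70.01, hence 71 as stated. 71 × 1.15 = 81.7, hence 82 as stated. I use 82 below. The documents give no QALY, utility or mortality figure.

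**Step 2. Each death interval under the rules**, assuming all earlier visits were made:

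| Death | Visits missing | Result under the rules |
|---|---|---|
| Before T1 | T1 to T4 | Discarded and replaced |
| T1 to T2 | T2, T3, T4 (three) | Discarded and replaced |
| T2 to T3 | T3, T4 (two, not more than two) | Kept; T4 = T2 value, T3 interpolated to the same value |
| T3 to T4 | T4 | Kept; T4 = T3 value |

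In the third row T4 must be filled first, because interpolating T3 needs a right-hand value. No row gives utility 0 after death.

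**Step 3. QALYs under assumed utilities.** Assumption, not from the documents: 0.30, 0.55, 0.62, 0.66 and 0.68 at T0 to T4, joined by straight lines. QALY is the area under the line in years.

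- Survivor: 0.25 × (0.425 + 0.585 + 0.640 + 0.670) = 0.580.
- Death at 1.5 months: true QALY 0.125 × (0.30 + 0.425)/2 = 0.045. The patient is replaced; with an average survivor the excess is 0.580 − 0.045 = 0.535.
- Death at 4.5 months: true QALY 0.106 + 0.125 × (0.55 + 0.585)/2 = 0.177. Replaced likewise, excess 0.403.
- Death at 7.5 months: true QALY 0.2525 + 0.125 × (0.62 + 0.64)/2 = 0.331. Scored 0.2525 + 0.5 × 0.62 = 0.562, excess 0.231.
- Death at 10.5 months: true QALY 0.4125 + 0.125 × (0.66 + 0.67)/2 = 0.496. Scored 0.4125 + 0.25 × 0.66 = 0.578, excess 0.082.

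**Step 4. Effect on the comparison.** With an assumed QALY SD of 0.20, the standard error of the difference is 0.20 × √(2/82) = 0.031. Three extra deaths in one service (3/82 = 3.7 percentage points) shift the difference by 3/82 × excess:

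| Time of death | Shift in QALY | In standard errors |
|---|---|---|
| 1.5 months | 0.020 | 0.6 |
| 4.5 months | 0.015 | 0.5 |
| 7.5 months | 0.008 | 0.3 |
| 10.5 months | 0.003 | 0.1 |

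For the earliest deaths, utility curves about 0.1 higher or lower together with an SD of 0.15 to 0.25 give 0.4 to 1.0 standard errors. The assumed T0 value matters little: setting it to 0 changes the excess at 1.5 months from 0.535 to 0.525.

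**Step 5. Direction of replacement.** Suppose 30% of patients are frail with utility 0.40 and the rest have 0.65, so the mean is 0.3 × 0.40 + 0.7 × 0.65 = 0.575. If 5% die before T2, all of them frail, and are replaced in proportion to those left, the analysed mean is (0.25 × 0.40 + 0.70 × 0.65)/0.95 = 0.584. The service with more early deaths looks better. These inputs too are assumptions, chosen to show direction.

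**The case against.** The strongest reply is that the article does not say deaths are drop-outs. The regime is introduced with drop-out and withdrawal, sits after the MANCOVA paragraph, and is not cited in the economic section. How death enters a QALY is detail that a full protocol or analysis plan could supply, and recording reasons for withdrawal should make deaths identifiable. This stands as a limit on certainty: applying the rules to deaths is an inference from the absence of any exception. It does not remove the point, because these are the only rules given for absent measurements, and a programmer following them would obtain the table in Step 2.

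A second reply concerns how many deaths there would be. Patients with ISS below 16 and complex limb or pelvic injuries were deliberately added, a rehabilitation indication is required, and consent precedes participation. These conditions probably keep many of the earliest deaths out of the cohort, and the earliest deaths produce the largest shifts. That also stands, and it is why the lower end of the range in Step 4 matters. The T0 utility is a further assumption, since the economic section states: "Assessments of the quality of life and costs will take place at T1 through T4".

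A reader might also infer that all costs run on to month 12 after a death. The documents do not support that. The regime does not say it covers costs. Table 2's note lists hospital database data as a source, and professionals record the hours spent on the intervention; both would stop at death. At most the point reaches cost-questionnaire and PRODISQ items, if the rules apply to them.

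**Conclusion.** The point holds in a bounded form. Applied as written, the rules drop and replace deaths before T2 and carry utility past later deaths, so death is never counted as QALY loss, and replacement can favour a service with more deaths.

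Two stronger readings should be resisted. One is that mortality cannot affect the result at all. It can, because replacement changes who is analysed (Step 5). The other is that the cost-utility ratio would take the wrong sign. That would require a known underlying QALY effect, which the documents do not give.

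The size is unknown. The article states no mortality, only 15% overall loss to follow-up, and nothing in it suggests that survival differs between the services. The figure of 0.003 to 0.020 QALY (0.1 to 0.6 standard errors) for three extra deaths among 82 rests on the assumed utility curve, a QALY SD of 0.20, replacement by an average survivor, and deaths between 1.5 and 10.5 months. This is a moderate issue that should be corrected because the correction is specific and nearly free.

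**What to change.** Add one paragraph to the analysis plan for the cost-utility analysis:

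- Keep every enrolled patient who dies, and exempt deaths from discard-and-replace, last-observation-carried-forward and interpolation.
- Use observed utility up to the date of death and 0 afterwards. State how the short stretch between the last measurement and death is valued, including for a death before T1.
- Carry no questionnaire-based costs or production losses forward past death; count them by the chosen costing method.
- Report deaths by service beside the FIM and SF-36 results, so that readers can see that those results describe survivors.

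The cost is recording the date of death and a slight fall in the QALY totals.

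### The cost sensitivity range of mean ± SD reflects patient spread rather than uncertainty in the mean, and the incremental costs and effects have no stated case-mix adjustment

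*Protocol article*

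**What the plan says.** The economic analysis is set out in the protocol article under Determination of costs.

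- **Main estimate.** "Ratios will be determined, based on incremental costs and effects of SFTRS compared to CTCS". The two ratios are cost per improvement on the FIM and net cost per QALY, over 12 months.
- **Sampling uncertainty.** "Bootstrap re-sampling techniques [46,47] are used to explore cost-effectiveness uncertainty".
- **Sensitivity analysis.** "Sensitivity analyses will be performed for the costs that turn out to have the largest impact on the differences in total costs" between the services. Both volumes and prices are to be considered, and the range of the uncertain factors "will be assessed by calculating a minimum and maximum (mean value of costs minus or plus the SD". The SD is not defined further.

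The design and the clinical analysis are described elsewhere in the article.

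- **Allocation.** Each group is recruited around a different trauma centre. The reason is distance, and the Population section concludes: "Therefore, a non-randomised controlled clinical trial is used".
- **Case mix.** Statistical analyses warns that in such studies "variations in case mix between centres can influence the interpretation of outcome data". It follows that, at T1 to T4, "differences in outcome variable between the 2 services will be tested using multiple MANCOVA's, entering various indicators of case mix as co-variates". The covariates are age, gender, ISS, number of complications and pre-trauma psychosocial status.
- **Place of costs.** Table 2 lists SF-36 and FIM as primary and HADS, MMSE and COPM as secondary outcomes. Costs appear only in a note below them.

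**The concern.** There are two separate problems, and both bear on the general research question of which service is more cost-effective from a societal point of view.

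First, cost-effectiveness depends on mean costs. A sensitivity range should therefore show how far a mean volume or a unit price could plausibly lie from the value used. A between-patient SD shows how much patients differ from one another, and it does not shrink as the sample grows. Costs are usually skewed, so the lower end can fall to zero or below. Almost any conclusion would look fragile under such a range, and the reader could not tell real fragility from an artefact of the rule.

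Second, the article names confounding by centre as a threat and gives a remedy for the clinical outcomes. It then describes the economic analysis, from increments to ratios, bootstrap and sensitivity analysis, without that remedy. If one region treats more severely injured patients, the raw cost difference includes that severity difference. Resampling the same patients reproduces the imbalance in every bootstrap sample. The results are meant to inform nation-wide introduction of the new service, so this matters.

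**Working it through.** **Sample size used.** The article gives no separate size for costs, so the FIM figures are used. The target difference is 0.15 × 30.2 = 4.53 points, with SD 9.5, two-sided 0.05 and 80% power. The normal approximation gives 70 per group. The t-test solution is 70.01, which rounds up to the stated 71. The stated 82 follows from 71 × 1.15 = 81.65.

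**Width of mean ± SD, read as the between-patient SD**

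The standard error of an arm mean is SD/√n, so one SD is √n standard errors. The 95% half-width is 1.96 × SD/√n. For a difference between arms it is 1.96 × SD × √(2/n).

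| | n = 71 | n = 82 |
|---|---|---|
| One SD, in standard errors of an arm mean (√n) | 8.4 | 9.1 |
| 95% half-width of an arm mean, in SD | 0.233 | 0.216 |
| One SD ÷ that half-width | 4.3 | 4.6 |
| 95% half-width of a difference, in SD | 0.329 | 0.306 |
| One SD ÷ that half-width | 3.0 | 3.3 |

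**Lower end of the range.** The article gives no cost mean or SD, so the coefficient of variation (CV) is an assumption. The planned minimum is (1 − CV) × mean. The lower 95% limit of the mean at n = 71 is (1 − 0.233 × CV) × mean.

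| Assumed CV | Planned minimum ÷ mean | Lower 95% limit ÷ mean |
|---|---|---|
| 0.5 | 0.5 | 0.88 |
| 1.0 | 0 | 0.77 |
| 1.5 | −0.5 | 0.65 |

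Any CV above 1 gives a negative cost.

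**Possible effect of unadjusted case mix.** If a factor related to cost differs between the centres by a standardised amount d and correlates r with cost, the raw cost difference shifts by about r × d cost SDs. The right yardstick is the standard error of the difference, SD × √(2/71) = 0.168 SD. The standard error of one arm mean would overstate the result by √2. All values of d and r below are assumptions.

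- d = 0.5, r = 0.3 to 0.5: the shift is 0.15 to 0.25 SD. Then 0.15/0.168 = 0.9 and 0.25/0.168 = 1.5 standard errors.
- d = 0.2 to 0.4, r = 0.2 to 0.5 (milder): the shift is 0.04 to 0.20 SD, or 0.24 to 1.19 standard errors. Coverage of a nominal 95% interval would be between 94.3% and 77.8%.

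**Which covariates can be used.** The listed covariates cannot all be carried over unchanged.

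- Age, gender and ISS are recorded on arrival at A&E in both groups (Demographic and medical variables).
- Number of complications is collected after the injury. The Introduction expects the new service to reduce secondary complications, so adjusting for it could remove part of the effect.
- Pre-trauma psychosocial status is recorded on admission to the rehabilitation centre. The description of conventional care allows patients to go instead to an outpatient clinic, a nursing home, a GP or a physiotherapist.

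**The case against.** The strongest reply has four parts.

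1. **The bootstrap already covers sampling uncertainty.** The SD range is a secondary step for selected cost items and changes neither the point estimate nor the bootstrap interval. This stands. A reader might infer that the uncertainty of the whole economic analysis is wrong, but the text does not support that.
2. **The SD is undefined.** For prices it could mean spread across centres or sources. This stands as a caveat. However, volumes come from patient-level forms and questionnaires, so the between-patient SD is the natural reading beside a mean cost. If another SD was meant, the text needs to say so.
3. **The article is condensed, and silence is not a statement that the increments are unadjusted.** The covariate analysis covers FIM and SF-36, which supply the effects. This stands in part: a fuller plan may extend the adjustment. But the article spells out the economic steps and places costs outside the listed outcomes. Tests at separate time points also do not by themselves yield adjusted 12-month costs, QALYs or ratios. A reader might conclude that the economic answer is wrong or fully confounded; that is not shown, because neither the size nor the sign of any bias can be found in the article.
4. **Negative ratios are not an error in the plan.** The article states "We hypothesise that SFTRS is associated with a reduction in health care and patient costs, and an improvement in quality of life", so a reader might object that the expected ratio is negative and cannot be ranked. Nothing in the text says that negative ratios will be ranked, and bootstrapped increments can show dominance directly. Net benefit and acceptability curves are a reporting choice.

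**Conclusion.** The point holds in two limited parts.

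- **The stated sensitivity range is unsuitable.** On the between-patient reading it is more than four times too wide as a 95% range for an arm mean, and it can include an impossible cost. The width depends only on that reading and on 71 to 82 patients per group. The negative minimum also needs a CV above 1, which the article neither gives nor excludes. The consequence is an uninformative sensitivity analysis, not a wrong main interval.
- **The economic comparison lacks the stated case-mix adjustment that the article itself considers necessary for the clinical outcomes.** This is a risk of bias of unknown size and direction. The 0.9 to 1.5 standard errors illustrate what plausible imbalances could do and are not an estimate for this trial.

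Both should be corrected, because they bear on the main research question and are cheap to change.

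**What to change.** 1. Replace mean ± SD by two ranges: the 95% bootstrap interval of the mean for each influential volume, and low and high values from a named source for each unit price.
2. State that incremental costs, FIM and QALYs are estimated by regression on service and case-mix covariates, refitted within each bootstrap sample, and that the ratios are formed from these adjusted increments.
3. Use the listed covariates that precede treatment and are recorded in both groups: age, gender and ISS. Add pre-trauma psychosocial status only if it is also available for conventional-care patients who never enter a rehabilitation centre. Leave out number of complications.

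Net benefit and an acceptability curve may be reported beside the ratios, but the correction does not depend on them.

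The cost is a few sentences and modest extra programming. No new data are needed with age, gender and ISS alone. Including psychosocial status could require collecting it in the hospital for the conventional group.
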